#### Recruitment

A multi-strategic approach to recruit Syrian refugees living in the urban area of Leipzig, German, will be targeted. This includes using established contacts as well as building new contacts with facilities frequented by Syrian refugees (e.g. refugee related clubs, associations and organizations, psychosocial centers, information centers, language schools, community colleges, universities, registration authorities, hospitals, clinics, primary care practices, psychotherapeutic practices, etc.). These facilities act as multipliers to reach out to potential study participants. Likewise, participants will be recruited from local reception centers and other forms of collective accommodation centers. We will use social media, instant messaging and online tools to spread information about the study. The local media will be involved. Bilingual flyers and posters will be displayed all across the city in appropriate public spots. During the recruitment phase, we will have an information booth at local events that might attract Syrian refugees. Importantly, since Syrian refugees are well connected with each other, we aim to reach additional participants of the Syrian community by using a snowball sampling approach, e.g. we ask participants to spread information about the study within their personal social network [29].

#### Allocation and randomization

Participants identified as eligible during screening will subsequently be randomly assigned to the IG or CG. Group assignment will follow a 1:1 ratio utilizing randomized permuted blocks of six, stratified by age and sex. This procedure ensures both balance in sample size across groups and control of important covariates. An external, independent statistician will generate the randomization block lists with a respective computer program (“blockrand”-package [40] written for R [41]). The different lists will be coded by this person so that the study coordinator, responsible for individual group allocation, remains blind to the lists’ strata identity.

#### Blinding

Besides randomization, the data analysts, who will conduct the primary analysis concerning the hypothesized group differences (IG vs. CG) in our primary and secondary outcome measures (see above), will be blind to group assignment.

#### Data collection

All assessments will be carried out in form of structured face-to-face interviews led by trained native Arabic speaking study nurses. The structured interviews will be present in form of paper-and-pencil assessments that the study nurses will complete to collect data on sociodemographics, primary and secondary outcomes using standardized questionnaires, as detailed above. Additionally, data will be collected to monitor possible negative effects and reasons for dropout (see below).

Data on the app usage will be collected through meta-data log-files that store anonymous information about the number of login-times and worked-through modules.

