#### Study adherence

Prior to randomization, participants will be pointed towards the required investment of time and effort necessary to complete the study in order to lower the risk for dropout.

Treatment adherence of the IG will be objectively assessed through the apps’ meta-data log-files that store information about the number of login-times and worked-through modules. Likewise, dropout assessment will be conducted to understand reasons for non-adherence.

Participants of both groups are assured to contact the study nurses in case of arising problems regarding current symptom burden, for example. Similar to the apps’ emergency button, the psychoeducational reading material will clearly state contact information regarding professional help in case of emergency.

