Healthcare resource use		x	only T2	yes
App usability (SUS)^a^		x	only T1	yes
User acceptance (TAM 3)^a^		x	only T1	yes

Note: ^a^to be assessed only in the intervention group

*DSI-SS* Depressive Symptomatology Index – Suicidality Scale [47], *PDS-5* Posttraumatic Diagnostic Scale for DSM-5 [30], *PHQ-9* Patient Health Questionnaire [31], *GAD* General Anxiety Disorder [48], *EQ-5D-5L* Euroqol Five Dimensions Questionnaire [49], *GSE* General Self-efficacy [50], *SSMIS-SF* Self-stigma of Mental Illness Scale – Short Form [51], *LSNS* Lubben Social Network Scale [52], *ESSI* Enriched Social Support Inventory [53], *PGI* Posttraumatic Growth Inventory [54], *RS-13* Resilience Scale [55], *Z-7* Zentralitätsskala [56], *SUS* System Usability Scale [36], *TAM-3* Technology Acceptance Model [37]

Ambiguous loss and prolonged grief - questions have been adapted from the German version of the Complicated Grief Inventory (ICG-D; [57]); Healthcare resource use – questionnaire was adapted from previous investigations and is available from the authors upon request [58]

We hypothesize that the app intervention reduces posttraumatic stress symptomatology (primary outcome), quantified using the Posttraumatic Diagnostic Scale for DSM-5 (PDS-5 [30]). The PDS-5 is a well-established self-report measure based on the diagnostic criteria of the DSM-5, which allows the assessment of posttraumatic stress symptom severity.

Regarding secondary outcomes, we moreover expect the intervention to reduce symptoms of depression, anxiety, and somatization. Positive intervention-related effects are also expected regarding quality of life, self-efficacy, perceived stigmatization, social support, ambiguous loss, and posttraumatic growth.

Use of resources in terms of health demands will be assessed using a cost book (bottom-up approach). Furthermore, we aim to gather information on user acceptance and usability of the self-help app using the System Usability Scale (SUS) [36] and Technology Acceptance Model (TAM3 [37]), respectively.

Last, meta-data stored in the app’s log-files will provide quantitative information about the use of the app, e.g. number of days used, number of worked-through modules, or operating time.

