#### Statistical analysis

All acquired data will be examined with respect to potential inconsistencies and missing values, which will be replaced using multiple imputation methods [42], if appropriate. To detect potential systematic biases, a drop-out analysis will be performed. Internal consistencies of the newly translated inventories will be calculated to evaluate their reliability. All subsequent analyses will be treated as intention-to-treat or completer-analyses. Data-analysts will be blinded for group allocation.

Changes in primary and secondary outcomes will be described using mean scores and standard deviations, among others. Short and medium termed treatment effects will statistically be inferred by using linear mixed effect models accounting for relevant covariates. Usability as well as user acceptance of the app will be evaluated using descriptive statistics. The significance level of all analyses will be set to *p* < 0.05.

To assess the potential health economic benefits, we will perform analyses of the (i) actual costs and (ii) the ICER of the intervention. Costs will be quantified by the frequency of how often physicians and therapists are consulted (including days spent in a hospital) and valuated using current standard costs [43]. The app development expenses will be treated as economically reasonable overhead costs and added accordingly. To assess the interventions’ economic efficiency, the ICER will be calculated as the ratio between the difference of the actual costs and the difference of the averaged treatment effects (indexed by either quality-adjusted life years or primary outcome scores) between IG and CG. Respective confidence intervals will be derived by non-parametric bootstrapping. To visualize the ICERs statistical uncertainty, cost-effectiveness-acceptance curves will be constructed, indicating the probability of an acceptable ICER in relation to willingness to pay for an effect. Alternatively, net benefit regressions [44] can be applied to estimate the respective group specific net benefits while accounting for potentially confounding variables such as age, sex, and education.

The results of the study will be reported according to the guidelines of the Consolidated Standards of Reporting Trials (CONSORT) statement [45].

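### Only the data analysts are stated to be blinded: nothing keeps the nurses who record the PDS-5 from learning the arm, and IG-only questionnaires fall in the same T1 assessment

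*Protocol article*

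**What the plan says.** Three parts of the protocol article bear on this.

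- **Who collects the outcomes.** Under Data collection: "All assessments will be carried out in form of structured face-to-face interviews led by trained native Arabic speaking study nurses". The same section describes "paper-and-pencil assessments that the study nurses will complete to collect data on sociodemographics, primary and secondary outcomes using standardized questionnaires". The nurse therefore both asks the questions and records the answers, for the primary outcome as well.
- **What the primary outcome is.** Under Outcomes: "The PDS-5 is a well-established self-report measure based on the diagnostic criteria of the DSM-5".
- **Who is blinded.** The Blinding section names "the data analysts, who will conduct the primary analysis concerning the hypothesized group differences" between the two arms and says that they "will be blind to group assignment". Statistical analysis repeats the point: "Data-analysts will be blinded for group allocation". Neither section mentions interviewers or participants.

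Table 1 restricts the SUS and TAM 3 to the IG. It schedules them at T1 and also marks them in the baseline (T0) column. Under Intervention, one arm receives an app log-in and the other a brochure, so participants know what they were given. Under Study adherence: "Participants of both groups are assured to contact the study nurses in case of arising problems".

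**The concern.** The PDS-5 score depends on what a participant chooses to say to a member of the project staff, and on how that person prompts, clarifies and writes down the answer. If the interviewer knows the arm, each of these steps can differ between arms. Any such difference is in the recorded score before the analyst sees it, so blinding the analyst gives no protection. Most secondary outcomes are collected in the same way. So are the effects used in the ICER, which is indexed by quality-adjusted life years or the primary outcome score.

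The Blinding section is present and says who is blinded, so the gap is not a detail that a condensed article leaves to a fuller document. As written, the protection covers the analysis and not the outcome interview.

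**Working it through.** **1. Can the interviewer learn the arm?**

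- All assessments are nurse-led interviews (Data collection), and the SUS and TAM 3 are assessments given to the IG only (Table 1). A nurse running a complete T1 assessment must know, or will find out, whether these forms apply. This is the one route that discloses the arm by its own content.
- The T0 mark in Table 1, if intended, would open the same route before treatment starts.
- Participants know their arm and could mention it. No instruction against this is described.
- The document describes no order of instruments within a visit and no separation of interviewers from arm-revealing tasks.
- The document does not say that the nurses are told the arm. The supported statement is that nothing prevents them from learning it.

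**2. The plan's own sample size.** Inputs from Sample size: d = 0.5, α = 0.05, power 0.90, 140 analysable, 40% dropout. The 1:1 ratio is from Allocation and randomization.

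- Two-sample t-test, one-sided α = 0.05: 69.2, rounded up to 70 per arm, 140 in total. This reproduces the stated figure.
- Two-sided α = 0.05: 85.03, rounded up to 86 per arm, 172 in total. With 140 the two-sided power is 83.6%. The document does not state sidedness, which is a separate point.
- Dropout: 140 / (1 − 0.40) = 233.3, rounded up to 234. This reproduces.

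**3. What an assumed shift would do.** Let b be an arm-related shift in the recorded score, in SD units, with no true effect. With n per arm and a two-sided t-test:

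- noncentrality δ = b·√(n/2)
- rejection rate = P(|T| > t₀.₉₇₅), where T is noncentral t with 2n − 2 degrees of freedom and noncentrality δ

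For n = 70, √35 = 5.916, with 138 degrees of freedom and a critical value of 1.977. The smallest significant difference is 1.977 × √(2/70) = 0.334 SD.

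| Assumed b | δ | Two-sided false-positive rate | Share of planned d = 0.5 |
|---|---|---|---|
| 0 | 0 | 5.0% | 0% |
| 0.1 SD | 0.592 | 9.0% | 20% |
| 0.2 SD | 1.183 | 21.7% | 40% |

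Tested one-sided, the reading under which 140 reproduces, the last two rates would be 14.5% and 32.0%.

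**4. Can sample size or analysis repair it?** No.

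- With 117 per arm (234 / 2), the two-sided rates are 11.9% at 0.1 SD and 33.1% at 0.2 SD. A larger sample detects the bias more reliably.
- Baseline adjustment sharpens the test against the shift as well. At 70 per arm and 0.2 SD, an assumed baseline correlation of 0.5 gives 27.4%.

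**The case against.** The strongest case on the other side is that the document never says the nurses know the arm. A reader might infer from the Blinding section that they are unblinded, but it is silent on them, and individual allocation is the coordinator's task. A reader might also infer that one nurse supports a participant and later interviews the same person. The text speaks only of study nurses and does not say so. Both objections stand, and neither reading is claimed here.

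Two other suggested routes to the arm are weak. Support contact is offered to both groups alike. The adverse-event question asks about trial participation in both arms. Neither discloses the arm by itself.

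A structured interview with fixed items limits interviewer discretion, and social desirability acts in both arms. Only a difference between arms biases the comparison. The control group also receives a substantial brochure with the same information as the app, which may narrow the difference in expectations. These points reduce the likely size of the bias but do not exclude it.

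The percentages in the working could be taken as this trial's expected error rate. The documents do not support that: b is assumed, and it combines interviewer bias with the reporting bias of participants who know their arm. Changing the interviewer's position would not remove the second part.

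Finally, a reader might see a contradiction between a self-report scale and an interview, and conclude that participants must complete the forms themselves. There is no contradiction, since a self-report scale can be read aloud. Self-completion would be a trade-off: literacy, mixed modes where help is needed, and prompt review of the suicidality and depression items.

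**Conclusion.** The point holds as a gap in protection. Interviewers of unstated blinding status record a subjective primary outcome, and IG-only instruments fall within the same T1 assessment. The only stated blinding applies after any bias would have entered the data.

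The size of the bias is unknown. Under an assumed arm-related shift of 0.1 to 0.2 SD, no true effect, 70 per arm and a two-sided 5% t-test, the false-positive rate would be about 9% to 22%. This illustrates how sensitive the trial is to such a shift. It is not an estimate, and not all of it could be recovered by the change below.

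This should be fixed. It concerns the primary outcome, cannot be corrected after data collection, and is cheap to reduce beforehand. It falls short of a fatal flaw because interviewer knowledge of the arm is inferred and the bias is assumed.

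**What to change.** - **Order of forms.** At T1 and T2, collect the PDS-5 first, then the other outcomes common to both arms. Give the SUS and TAM 3 last at T1, on a separate form, by a nurse other than that participant's T2 interviewer, so that T1 does not disclose the arm for T2. Confirm or remove the T0 mark for these two instruments in Table 1. If it stands, the nurse who gives them at T0 should not do that participant's T1 or T2 interview.
- **Interviewers.** Within the existing team, assign each T1 and T2 interview to a nurse who is not told the arm and who has taken no part in handing out log-ins or brochures or in that participant's support contacts.
- **Participants.** Ask them before each interview not to say which arm they are in.
- **Text.** Extend the Blinding section to the outcome interviewers, and state that participants are not blinded.

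Leave the nurse support contact route and the review of suicidality items unchanged.

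The cost is scheduling work within the nurse team. No extra assessor, instrument or participant is needed. Blinding may be imperfect because participants know their arm, and their own reporting bias will remain and should be acknowledged.

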#### Data management

Data entry will take place successively and timely after collection using a statistical package. However, a data completeness and consistency check will take place beforehand. In case of missing answers to items, reasons for missing information will be clarified and efforts undertaken to reach completion. De-identified data will be entered in a data mask which will be password-protected and stored locally, with access granted only to study personnel who have signed data protection wavers. Anonymous log-file data of app usage will be collected, stored and transferred using SSL-technology to ensure data encryption and protection. In fact, specific arrangements regarding data protection (e.g. separation of evaluation and program, no real names for program login) will be defined by a separate data protection concept.

#### Statistical analysis

All acquired data will be examined with respect to potential inconsistencies and missing values, which will be replaced using multiple imputation methods [42], if appropriate. To detect potential systematic biases, a drop-out analysis will be performed. Internal consistencies of the newly translated inventories will be calculated to evaluate their reliability. All subsequent analyses will be treated as intention-to-treat or completer-analyses. Data-analysts will be blinded for group allocation.

Changes in primary and secondary outcomes will be described using mean scores and standard deviations, among others. Short and medium termed treatment effects will statistically be inferred by using linear mixed effect models accounting for relevant covariates. Usability as well as user acceptance of the app will be evaluated using descriptive statistics. The significance level of all analyses will be set to *p* < 0.05.

To assess the potential health economic benefits, we will perform analyses of the (i) actual costs and (ii) the ICER of the intervention. Costs will be quantified by the frequency of how often physicians and therapists are consulted (including days spent in a hospital) and valuated using current standard costs [43]. The app development expenses will be treated as economically reasonable overhead costs and added accordingly. To assess the interventions’ economic efficiency, the ICER will be calculated as the ratio between the difference of the actual costs and the difference of the averaged treatment effects (indexed by either quality-adjusted life years or primary outcome scores) between IG and CG. Respective confidence intervals will be derived by non-parametric bootstrapping. To visualize the ICERs statistical uncertainty, cost-effectiveness-acceptance curves will be constructed, indicating the probability of an acceptable ICER in relation to willingness to pay for an effect. Alternatively, net benefit regressions [44] can be applied to estimate the respective group specific net benefits while accounting for potentially confounding variables such as age, sex, and education.

The results of the study will be reported according to the guidelines of the Consolidated Standards of Reporting Trials (CONSORT) statement [45].

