#### Sample size

Anticipated sample size was calculated based on recent research evaluating the efficacy of telemedical-based treatment of posttraumatic stress symptoms [20, 21, 38]. Given a moderate between-group effect at T1 (Cohen’s *d* = 0.5), a significance level of *α* = 0.05 and a statistical power of 1-*β* = 0.90, optimal sample size for estimating a significant treatment effect is *n* = 140. Expecting a drop-out rate of approximately 40% (e.g. due to change in residence status), *n* = 94 participants have to be included additionally, yielding an ideal baseline sample of *n* = 234 participants at T0 [39].

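### Every analysis, including the primary PDS-5 test, may be intention-to-treat or completer with neither ranked first, although about 40% dropout is expected

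*Protocol article*

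**What the plan says.** The Statistical analysis section of the protocol article fixes the analysis population for everything that follows it: "All subsequent analyses will be treated as intention-to-treat or completer-analyses". The same section adds "Short and medium termed treatment effects will statistically be inferred by using linear mixed effect models accounting for relevant covariates" and "The significance level of all analyses will be set to *p* < 0.05". Missing values are to be multiply imputed where that is judged appropriate, a drop-out analysis is to look for systematic bias, and the analysts are blinded to group.

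The Outcomes section states the primary hypothesis: "We hypothesize that the app intervention reduces posttraumatic stress symptomatology (primary outcome), quantified using the Posttraumatic Diagnostic Scale for DSM-5". It attaches no time point. The Sample size section does use one: "Given a moderate between-group effect at T1". It also reads "Expecting a drop-out rate of approximately 40" per cent, which takes 140 evaluable participants to 234 at baseline.

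**The concern.** This is not detail left to an analysis plan. The article states the analysis population, and states it as an unranked either/or. An analysis plan that named one population as primary would have to override that sentence.

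Two things are at stake. First, completing the study happens after randomisation. If the reasons for staying differ between an interactive app and a brochure, completers in the two arms are no longer comparable. The article itself makes differential retention plausible: the Background suggests that easy access to apps may help adherence, and the section on expected benefits and harms warns that trauma-related content may at first stir up distressing memories. Second, if both analyses are run and either may be headlined, the test has two chances at 5%.

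**Working it through.** **1. The plan's own figures.** Inputs from Sample size: d = 0.5, α = 0.05, power 0.90, dropout 40%.

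- A two-sample t-test at one-sided 0.05 needs 69.2, so 70 per arm and 2 × 70 = 140, which matches. At two-sided 0.05 it needs 85.03, so 86 per arm and 172. The article does not state sidedness; that is a separate matter.
- Dropout: 140 / (1 − 0.40) = 233.3, so 234, which matches. The added 94 are 94 / 234 = 40.2% of the baseline sample. A completer analysis could therefore leave out up to two-fifths of those randomised.

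**2. False-positive rate if either population may be chosen.** For two two-sided 5% tests with null correlation ρ, the rate is 1 − P(|Z1| < 1.96 and |Z2| < 1.96), with Z1 and Z2 bivariate normal. The documents give no ρ, so it is assumed.

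| ρ between the two tests | At least one significant |
|---|---|
| 0.95 | 0.065 |
| 0.90 | 0.070 |
| 0.85 | 0.075 |

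The range is reasonable. When one sample is nested in the other and dropout is random, ρ is the square root of the ratio of sample sizes. With 80% seen at T1 and 60% completing, ρ = √(0.60 / 0.80) = 0.87. A null simulation of that case (117 per arm, 6,000 runs, visit correlation 0.5 or 0.7) gave about 0.05 for each test alone and 0.0725 to 0.074 when either could count.

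**3. What selection can do, and what the all-randomised analysis recovers.** The same simulation was run with no true effect and these assumptions: about 40% dropout in each arm, about half of the dropouts still giving a T1 value, brochure dropout random, and app dropout more likely with less improvement (log-odds 0.5 or 1.0 per SD of change). Rejection rates at T1, adjusted for baseline:

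| Visit correlation, log-odds | Completers only | All available at T1 | Full data |
|---|---|---|---|
| 0.5, 0.5 | 0.171 | 0.071 | 0.050 |
| 0.5, 1.0 | 0.433 | 0.115 | 0.053 |
| 0.7, 0.5 | 0.190 | 0.074 | 0.042 |
| 0.7, 1.0 | 0.479 | 0.130 | 0.053 |

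Using everyone with a T1 value removes much of the inflation but not all of it. The mechanism is one-sided by assumption; with random dropout neither analysis is biased.

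**4. Limit of the gain.** The benefit depends on why people leave and what was recorded before they left. In a second illustrative simulation, an all-randomised analysis cut the bias from about 0.18 to 0.01 SD when dropout depended on baseline, and from about 0.28 to 0.19 SD when it depended on the T1 outcome. The first of these gains is against a completer comparison not adjusted for baseline; a baseline-adjusted completer model would share it. Where dropouts have no T1 value and leave for reasons unrelated to baseline, the all-randomised analysis gains nothing.

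**The case against.** **Safeguards.** Analysts are blinded, a drop-out analysis is planned, imputation is foreseen and reasons for dropout are collected. The sentence may also mean that both analyses will be run. All of this lowers the risk, but none of it settles which result is primary. A blinded analyst can still see which analysis gives the smaller p-value, the drop-out analysis has no stated consequence, and a decision on imputation taken after inspecting the missing data is not a prior choice. If both analyses are meant, a ranking is all that is needed.

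**Dropout may be unrelated to arm.** The reasons the article offers (residence status, contact barriers, deportation) have no evident link to allocation. That is fair, and is why the bias is described as possible. Those reasons are given as examples only.

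**Two stronger readings that the documents do not support.** A reader might infer that T1 and T2 are two chances at the primary claim, with further error inflation. No passage says that success at either visit counts. The sample size is tied to T1, the Timeline gives T2 a separate medium-term purpose, and the Discussion expects benefit over four weeks. T1 is implied as primary, and only the label is absent.

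A reader might also take 0.40 × an assumed gap of 0.3 to 0.5 SD between app dropouts and app completers, which is 0.12 to 0.20 SD, as the price of choosing completers over intention-to-treat. It is not. When that gap is unrelated to baseline and T1 is missing, imputation in all randomised participants carries the same bias. The figure is a cost of informative dropout, not of the sentence at issue.

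**Conclusion.** The point holds for the analysis population. The article permits either population for the primary test, ranks neither, and expects about 40% dropout. The efficacy claim could therefore rest on a comparison that randomisation no longer protects, or on the better of two results. Free choice alone raises the type I error from 5% to about 6.5% to 7.5%, assuming two-sided tests and correlations of 0.95 to 0.85.

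Selection bias in the completer comparison could matter more, but its size cannot be read from the documents. The rejection rates of 0.17 to 0.48 rest wholly on an assumed app-arm dropout mechanism. An all-randomised analysis addresses dropout explained by observed data, and leaves bias from dropout that depends on unobserved outcomes.

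**What to change.** Replace the either/or sentence with one primary test: the difference between intervention and control group in PDS-5 at T1, in all randomised participants as allocated, from the linear mixed model with baseline PDS-5 and all available data. Multiple imputation that includes arm, baseline and visit is an acceptable alternative, provided one of the two is named in advance. State that the completer analysis is supportive only, and label the T2 comparison as secondary.

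Optional: a delta-shift sensitivity analysis, which makes imputed outcomes of dropouts progressively worse and reports where the conclusion changes. It addresses the part of the bias that the primary analysis cannot remove.

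The cost is two or three sentences, plus one further analysis if the option is taken. Design, sample size and data collection do not change. What is given up is the freedom to headline the completer result.

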## Discussion

We aim to develop and evaluate an interactive self-help app in Arabic for Syrian refugees with symptoms of posttraumatic stress. We expect that the use of our self-help app will lower respective and associated comorbid symptoms, e.g. depression or anxiety, over a course of four weeks. Moreover, our evaluation will consider the intervention’s cost-effectiveness as well as aspects regarding usability and user acceptance. We plan to make the app publicly available. Hence, we hope to provide a flexible low-threshold treatment for Syrian refugees, who suffer from the consequences of traumatization, but who may lack access to an appropriate treatment. If proven to be efficient, the self-help app could fill an important treatment gap in health services provision to a large group in need, and thus, could significantly improve the psychosocial care for Syrian refugees in Germany. Moreover, after implementation in public health, applicability may not only be restricted to Syrian refugees, but the app can be helpful for refugees from other Arabic-speaking countries with similar cultural backgrounds.

However, the realization of the project might be subject to some risks that have to be considered. Regarding the app development, it is important to adequately adapt the content to culture-sensitive aspects (e.g. disease concepts, the specific situation of refugees in Germany). Therefore, insights obtained from interviews with respective focus groups will be integrated. While the translation of the app materials and research inventories need to be culturally sensitive, it should not lose the necessary precision. In order to optimally balance these demands, we will cooperate with qualified translators, bilingual and native Arabic speaking experts, who will translate and review all materials within the standard forward and backward translation process (TRAPD-Model). Lastly, difficulties might occur with respect to recruitment and adherence of participants, e.g. due to contact barriers, dropout, or imminent deportation. We therefore aim for a multi-strategic recruitment approach. In addition, we applied a high dropout rate (40%) for sample size calculation.

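### One p < 0.05 rule covers all analyses, so any of nine hypothesised secondary outcomes could be declared an effect even if the primary outcome (PDS-5) is null

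*Protocol article*

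**What the plan says.** The protocol article names one primary outcome, posttraumatic stress symptoms on the PDS-5. For secondary outcomes, the Outcomes section states two sets of directional expectations:

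- Three symptom reductions: "Regarding secondary outcomes, we moreover expect the intervention to reduce symptoms of depression, anxiety, and somatization".
- Six further benefits: "Positive intervention-related effects are also expected regarding quality of life, self-efficacy, perceived stigmatization, social support, ambiguous loss, and posttraumatic growth".

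The Discussion repeats the expectation for depression and anxiety over the four-week course.

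Under Blinding, the primary analysis is described as covering the hypothesised differences between arms in both the primary and the secondary measures. Under Statistical analysis, one paragraph deals with primary and secondary outcomes together: "Short and medium termed treatment effects will statistically be inferred by using linear mixed effect models accounting for relevant covariates". The Timeline section places T1 directly after the one-month intervention and T2 three months after it. The same paragraph then sets the error rule: "The significance level of all analyses will be set to" p < 0.05.

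The article nowhere makes the secondary tests conditional on the PDS-5 result, and nowhere describes them as supportive or exploratory.

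**The concern.** The nine secondary outcomes are planned as hypothesis tests. They have a stated direction, the same type of model as the PDS-5 and the same threshold. The threshold controls the error of each test at 5%, but not the chance that at least one of the nine comes out significant when the app does nothing.

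What is at stake is the wording of conclusions. If the PDS-5 shows no difference, the rule as written still lets the report say that the app improves, for example, self-efficacy or social support at the trial's significance level. The Dissemination policy section plans to reach a large health insurer, national institutions and the public media. Those readers would have no means of telling a chance result from a confirmed one.

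**Working it through.** The article gives no family-wise error rate, so there is no figure of its own to reproduce.

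**Inputs from the article**
- Threshold: 0.05 for all analyses (Statistical analysis).
- Hypothesised secondary outcomes: 3 + 6 = 9 (Outcomes).
- Follow-up times at which effects are inferred: 2, T1 and T2 (Timeline; Statistical analysis).

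**Assumptions, because the article does not give them**
- Tests are two-sided.
- The app has no effect on any of the nine outcomes (global null).
- Test statistics are jointly normal, with the same correlation r between any two outcomes, r from 0 to 0.7.
- Correlation w between the T1 and T2 statistics of one outcome is 0 to 0.8. The correlation between different outcomes at different times is r × w.
- Either one test per outcome (9 tests) or separate T1 and T2 tests (9 × 2 = 18 tests).

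**Independent tests, closed form**

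For k independent tests, P(at least one p < 0.05, either direction) = 1 − 0.95^k.
- k = 9: 1 − 0.95^9 = 0.370
- k = 18: 1 − 0.95^18 = 0.603

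A false result favouring the app has probability 0.025 per two-sided test, so P = 1 − 0.975^k.
- k = 9: 1 − 0.975^9 = 0.204
- k = 18: 1 − 0.975^18 = 0.366

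**Correlated tests, simulation (400,000 draws per setting, critical value 1.96)**

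| r between outcomes | 9 tests, favours app | 9 tests, either direction | 18 tests, favours app (w 0.5 to 0.8) | 18 tests, either direction (w 0 to 0.8) |
|---|---|---|---|---|
| 0 | 20% | 37% | 34% to 30% | 60% to 52% |
| 0.3 | 17% | 33% | 28% to 24% | 55% to 46% |
| 0.5 | 13% | 27% | 23% to 20% | 47% to 39% |
| 0.7 | 10% | 20% | 17% to 15% | 36% to 30% |

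The 34% at the top of the favourable 18-test column takes w = 0.5. With w = 0 as well as r = 0 it is the 37% of the closed form.

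**Benchmark.** A single two-sided 5% test gives a false result favouring the app 2.5% of the time. The lowest figure with one test per outcome, 10%, is about 10/2.5 = 4 times that. The highest, 20%, is about 20/2.5 = 8 times.

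**Sidedness.** The article does not state it. One-sided tests at 0.05 would give about 18-37% with 9 tests and 25-60% with 18.

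**The case against.** The strongest reply is that this is only silence. The article condenses a fuller plan, and handling of multiplicity among secondary outcomes is commonly left to the analysis plan. A threshold of 0.05 does not even exclude adjustment, since adjusted p-values are also compared with 0.05. Silence alone would indeed be no finding. But the article does more than stay silent: it states one rule for every analysis and places the secondary hypotheses beside the primary one. Nothing in that rule limits what a secondary p-value below 0.05 may be taken to show.

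A second reply is that unadjusted secondary outcomes are ordinary practice. That stands where they are presented as supportive, and the fix below asks for no more than that.

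Three stronger readings are tempting, and the article does not support them:

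- **That 30-60% of null trials would show a false benefit.** That range needs 18 separate two-sided tests, and it also counts results against the app. The article says only that mixed models will be used for short- and medium-term effects. It does not say that each outcome gets two tests. Going to 22 tests by adding the social network and religious belief scales in Table 1 reaches further still, because no effect is predicted for either.
- **That the outcomes are unranked.** PDS-5 is the single named primary outcome and the others are labelled secondary. What is missing is any consequence of that ranking for the error rule.
- **That a chance secondary result would trigger release of the app.** The Abstract and the Dissemination policy section plan free release without a significance condition. The Discussion's conditional remark about filling a treatment gap names no secondary outcome as sufficient proof.

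**Conclusion.** The point holds as a modest one. The stated rule lets a secondary effect be declared at the trial's significance level when the PDS-5 is null. Under a global null with two-sided 5% tests, the chance of at least one false secondary result favouring the app is about 10-20% with one test per outcome and about 15-34% with T1 and T2 tested separately. In either direction it is about 20-37% and 30-60%.

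These sizes rest on assumed correlations, an assumed number of tests and assumed two-sidedness, none of which the article fixes. The conclusion does not depend on the choice: the lowest value in the range is about four times what one such test would give. The PDS-5 lies outside this family, so its error rate and power are not touched.

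**What to change.** In the Statistical analysis section, replace the rule for all analyses with wording such as:

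> The p < 0.05 decision rule applies to the PDS-5 efficacy test. Secondary outcomes are supportive and will be reported as estimated group differences with 95% confidence intervals, without claims of demonstrated effect.

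A formal scheme, such as Holm adjustment or a fixed testing order after a significant PDS-5 result, is a matter of preference. It is needed only if the investigators want a confirmatory secondary claim.

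The cost is one or two sentences, with no extra participants, visits or data. The downside is that an isolated secondary p-value below 0.05 can no longer be presented as a demonstrated effect.
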